## STUDY SYNOPSIS

|                                 |                                                                                                                                                                                                                                                                                                                                                                                                                                                                                                                                                                                                                                                                                                                                                                   |
|---------------------------------|-------------------------------------------------------------------------------------------------------------------------------------------------------------------------------------------------------------------------------------------------------------------------------------------------------------------------------------------------------------------------------------------------------------------------------------------------------------------------------------------------------------------------------------------------------------------------------------------------------------------------------------------------------------------------------------------------------------------------------------------------------------------|
| Sponsor / Sponsor-Investigator: | Xijing Hospital, The Forth Military Medical University-[name], MD, PhD
(investigator-initiated trial)                                                                                                                                                                                                                                                                                                                                                                                                                                                                                                                                                                                                                                                 |
| Study Title:                    | Effect of cerebellar stimulation on the awareness recovery in disorders of consciousness                                                                                                                                                                                                                                                                                                                                                                                                                                                                                                                                                                                                                                                                          |
| Short Title / Study ID:         | CARE-DOC                                                                                                                                                                                                                                                                                                                                                                                                                                                                                                                                                                                                                                                                                                                                                          |
| Protocol Version and Date:      | V1.0, March 2022                                                                                                                                                                                                                                                                                                                                                                                                                                                                                                                                                                                                                                                                                                                                                  |
| Trial registration:             | www.clinicaltrial.gov NCT05558930                                                                                                                                                                                                                                                                                                                                                                                                                                                                                                                                                                                                                                                                                      |
| Study design:                   | A randomized, double-blind, sham-controlled, crossover trial                                                                                                                                                                                                                                                                                                                                                                                                                                                                                                                                                                                                                                                                                                      |
| Objective(s):                   | To evaluate the effects of cerebellar intermittent theta burst stimulation (iTBS) in promoting consciousness recovery in patients with disorders of consciousness (DoC)                                                                                                                                                                                                                                                                                                                                                                                                                                                                                                                                                                                           |
| Primary outcome (s):            | 
 
The difference in the change of Coma Recovery Scale-Revised (CRS-R) scores between the iTBS and sham stimulation groups after the 5-session treatment
 
                                                                                                                                                                                                                                                                                                                                                                                                                                                                                                                                                           |
| Secondary outcome (s):          | 
 
The between-group differences in the “ABCD” EEG patterns after the fifth session of stimulation.
 
The Glasgow Outcome Scale-Extended (GOS-E) scores of all the participants after 3 months and 6 months of enrollment
 
                                                                                                                                                                                                                                                                                                                                                                                                                                                                                   |
| Inclusion / Exclusion criteria: | 
Inclusion:
 
 
Vegetative state (VS) / unresponsive wakefulness syndrome (UWS) or minimally conscious state (MCS) according to at least two CRS-R assessments
 
Age <math>\geq 18</math> years
 
Written informed consent obtained from legal surrogates
 
 
Exclusion:
 
 
Patients in coma
 
Brain injury <math>< 1</math> week
 
Presence of metallic hardware in close contact with the discharging coil (such as cochlear implants, an Internal Pulse Generator or medication pumps)
 
Patients with high risks according to standard questionnaire to screen transcranial magnetic stimulation (TMS) candidates
 
 |
| Measurements and procedures:    | Eligible patients will receive bilateral cerebellar iTBS and sham stimulation once daily for 5 consecutive days, either iTBS stimulation first or sham stimulation first,                                                                                                                                                                                                                                                                                                                                                                                                                                                                                                                                                                                         |

|                        |                                                                                                                                                                                                                                                                                                                                                                                                                                                                                                                                                                                        |
|------------------------|----------------------------------------------------------------------------------------------------------------------------------------------------------------------------------------------------------------------------------------------------------------------------------------------------------------------------------------------------------------------------------------------------------------------------------------------------------------------------------------------------------------------------------------------------------------------------------------|
|                        | 
separated by a 5-day washout period. Demographic, MRI and clinical information are collected at enrolment. The level of consciousness is assessed with CRS-R before and after each stimulation session within 2 hours.
 
Additionally, 32-channel EEG will be performed 20 minutes before and after the first and after the fifth treatment sessions within 30 minutes.
 
Analyses will compare the effects of iTBS and sham stimulation on the CRS-R score and EEG and assess the functional outcomes of all the participants 3 months and 6 months after enrolment.
 |
| Study Intervention:    | Bilateral cerebellar iTBS stimulation under neuronavigation                                                                                                                                                                                                                                                                                                                                                                                                                                                                                                                            |
| Number of Participants | 44                                                                                                                                                                                                                                                                                                                                                                                                                                                                                                                                                                                     |

## ABBREVIATION

|         |                                              |
|---------|----------------------------------------------|
| AC      | Academic Committee                           |
| AE      | adverse event                                |
| CLMM    | cumulative link mixed effects model          |
| CRF     | case report form                             |
| CRS-R   | Coma Recovery Scale-Revised                  |
| DSMB    | Data and Safety Monitoring Board             |
| DoC     | disorders of consciousness                   |
| DLPFC   | dorsolateral prefrontal cortex               |
| DSMB    | Data and Safety Monitoring Board             |
| EEG     | electroencephalography                       |
| EMCS    | emergence from MCS                           |
| EC      | Ethics Committee                             |
| EC      | Executive Committee                          |
| FFT     | fast fourier transform                       |
| GLM     | generalized linear model                     |
| GPI     | globus pallidus interna                      |
| HF-rTMS | high-frequency rTMS                          |
| ICA     | independent component analysis               |
| ITT     | intention-to-treat                           |
| iTBS    | intermittent theta burst stimulation         |
| IQR     | interquartile range                          |
| LOCF    | last observation carried forward             |
| LMM     | linear mixed model                           |
| MRI     | magnetic resonance imaging                   |
| MCS     | minimally conscious state                    |
| PP      | per-protocol                                 |
| PPC     | posterior parietal cortex                    |
| PSD     | power spectral density                       |
| PI      | principal investigator                       |
| rTMS    | repetitive transcranial magnetic stimulation |
| RMT     | resting motor thresholds                     |
| SAE     | serious adverse event                        |
| SAP     | statistical analysis plan                    |
| SCS     | spinal cord stimulation                      |
| SD      | standard deviation                           |
| GOS-E   | Glasgow Outcome Scale-Extended               |
| tDCS    | transcranial direct current stimulation      |
| TMS     | transcranial magnetic stimulation            |
| TBI     | traumatic brain injury                       |
| UWS     | unresponsive wakefulness syndrome            |
| VNS     | vagus nerve electrical stimulation           |
| VS      | vegetative state                             |

## 1 STUDY FLOW CHART

[figure not shown]

**Flow chart:** iTBS=intermittent transcranial magnetic stimulation; stim=stimulation

## 2 BACKGROUND

Disorders of consciousness (DoC) are characterized by alterations in arousal and/or awareness and are caused by severe brain injuries that disrupt the functional connectivity of corticothalamic system and its connection between basal ganglia and limbic system, to weaken or stop the excitatory synaptic activity in the cerebral cortex. Cardiac arrest, traumatic brain injury (TBI), intracerebral hemorrhage, and ischemic stroke are common causes of DoC. Patients who survive coma after the acute stage of brain injury but still do not awaken often step into a phase of VS/UWS (arousal without awareness) or minimally conscious state (MCS) (minimal, reproducible but inconsistent awareness).

### **Lack of evidently effective treatment for recovery of patients with DoC**

Pharmacological treatments that focused on promoting dopamine signaling, such as amantadine, methylphenidate, levodopa, bromocriptine, and subcutaneous apomorphine, have been tested in previous trials to promote recovery in patients with DoC. However, only amantadine has been confirmed to have some effect on restoring consciousness in patients with VS/UWS and MCS 4-16 weeks after acute brain injury. Still, the actual clinical efficacy is not satisfactory. Electrophysiological interventions such as deep brain stimulation, TMS, transcranial direct current stimulation (tDCS), low-frequency focused ultrasound, vagus nerve electrical stimulation (VNS) and spinal cord stimulation (SCS), may promote recovery in patients with subacute to chronic DoC in some trials with varying effects, but it seems difficult to get consistent evidence of efficacy in different study populations. For example, tDCS was shown to benefit patients with MCS in a randomized controlled trial in 2014, but was recently confirmed to be of no benefit in either MCS or UWS.

### **Transcranial magnetic stimulation: a feasible treatment approach**

Transcranial magnetic stimulation is widely considered to be a safe, convenient and effective method to induce excitability changes in brain activity. Repetitive transcranial magnetic stimulation (rTMS) can modulate cortical activity via long-term potentiation and long-term depression to treat neurological and psychiatric disorders, such as Parkinson's disease, stroke, epilepsy, Alzheimer's disease, depression, schizophrenia, etc. In recent ten years, the conscious promoting effect of rTMS in patients with MCS and/or UWS has been tested in clinical trials, mostly targeting the left M1, and the left or right dorsolateral prefrontal cortex (DLPFC) with high-frequency stimulation to produce a brain excitation effect and induce long-term potentiation-like plasticity. M1 and DLPFC seem to have shown conscious restoring efficiency in some trials, but they lack consistent and convincing results in different study populations because the specific mechanism underlying the function is unclear. A recent study showed that rTMS over the posterior parietal cortex (PPC) can be used to treat patients with DoC; however, the efficacy requires further studies. Besides the high-frequency stimulation, iTBS, another more efficient and time-saving stimulation, has been used in a small sample of patients with DoC and resulted in both clinical

behavioral and neurophysiological improvement. Importantly, no serious side effects have been reported in most previous studies.

### **Cerebellum is a promising target for improving recovery of consciousness in patients with DoC**

According to the mesocircuit model, all severe brain injuries that cause leading to coma share a common pathological substrate, which is a marked loss of background synaptic activity owing to either widespread neocortical, striatal, and thalamic neuronal death, dysfunction or disconnection, or focal injury to the paramedian mesodiencephalon (i.e., the central thalamus and rostral brainstem tegmentum). Widespread disfacilitation occurs, involving neocortical, striatal, and thalamic neurons, with a specific contribution from central thalamic neurons that integrate the loss of input from multiple cerebral targets. Loss of medium spiny neurons inhibition of the globus pallidus interna (GPi) produces active inhibition of components of the central thalamus, including the central lateral nucleus. Together, these mechanisms are proposed to produce a downregulation of activity across the anterior forebrain, resulting in limited or fluctuating behavioral responsiveness.

The cerebellum is well known for coordinating motor function and balance control; besides, it is also involved in non-motor functions, such as cognitive and executive functions, memory, learning, language, et al, and consciousness. The cerebellar hemisphere is divided into 10 lobes, and the dentato-rubro-thalamic tract is the main tract connecting the cerebellum and cerebral cortex with lobe VII located in the posterior part as the cardinal afferent area. Functional connectivity reveals that lobe VII is mainly mapped to frontoparietal network of cerebral cortex.

Considering the topography of the frontoparietal network in the cerebellum and the cortex-cerebellar pathway, lobe VII may be a candidate target to modulate the brain network in patients with DoC.

In the present study, we conduct a randomized, double-blind, cross-over trial to explore the consciousness-restoring efficacy and brain function-modulating effect of cerebellar iTBS in patients with DoC.

## **3 STUDY OBJECTIVES**

### **3.1 Primary objective(s)**

- To evaluate the effect of 5-session bilateral cerebellar iTBS stimulation on promoting consciousness recovery in patients with DoC.

### **3.2 Secondary objective(s)**

- To evaluate the effects of cerebellar iTBS on EEG after five treatment sessions.
- To assess the functional outcomes of all the participants at 3 months and 6 months after enrolment.

### **3.3 Safety outcome(s)**

Safety outcomes included adverse events, including intolerance to TMS, and severe adverse events. The common adverse effects of TMS include dizziness, headache, tinnitus, and tingling or burning sensation on the scalp, which usually ease spontaneously without symptomatic treatment. Any uncomfortable condition due to the iTBS stimulation and needs to be eased by down-regulating stimulus intensity or discontinuation of stimulation are seen as intolerance. Rare adverse effect of TMS includes seizures, for which physicians will administer appropriate symptomatic treatment.

A Serious Adverse Event (SAE) is defined as any event that:

- requires inpatient treatment not envisioned in the protocol or extends a current hospital stay;
- results in permanent or significant incapacity or disability;
- is life-threatening or results in death;
- causes a congenital anomaly or birth defect.

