## **4 STUDY DESIGN**

### **4.1 General study design**

This is a randomized, double-blind, crossover trial. Patients will be randomly assigned to the iTBS stimulation-first group or the sham stimulation-first group after the 5-day baseline assessments (see section 7). During each treatment session, patients will receive either iTBS stimulation or sham stimulation once daily for 5 consecutive days. The two treatment sessions are separated by a 5-day washout period. Demographic, MRI, and clinical information of the patients will be collected at enrolment. The CRS-R score will be assessed before and after every session of iTBS and sham stimulation within 2 hours. 32-channel EEG will be performed 20 minutes before and after the first and after the fifth treatment sessions within 30 minutes. The analyses will compare the effects of iTBS and sham stimulation on the CRS-R score and EEG and assess the functional outcomes of all the participants 3 months and 6 months after enrolment. The TMS deliverer is the only investigator who is aware of the grouping results and is required to sign the confidentiality agreement. All other investigators, including attending physicians, nurses, clinical score raters, EEG analysts, and statisticians, are blinded to the allocation.

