### **3.3 Safety outcome(s)**

Safety outcomes included adverse events, including intolerance to TMS, and severe adverse events. The common adverse effects of TMS include dizziness, headache, tinnitus, and tingling or burning sensation on the scalp, which usually ease spontaneously without symptomatic treatment. Any uncomfortable condition due to the iTBS stimulation and needs to be eased by down-regulating stimulus intensity or discontinuation of stimulation are seen as intolerance. Rare adverse effect of TMS includes seizures, for which physicians will administer appropriate symptomatic treatment.

A Serious Adverse Event (SAE) is defined as any event that:

- requires inpatient treatment not envisioned in the protocol or extends a current hospital stay;
- results in permanent or significant incapacity or disability;
- is life-threatening or results in death;
- causes a congenital anomaly or birth defect.

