## **4 STUDY DESIGN**

### **4.1 General study design**

This is a randomized, double-blind, crossover trial. Patients will be randomly assigned to the iTBS stimulation-first group or the sham stimulation-first group after the 5-day baseline assessments (see section 7). During each treatment session, patients will receive either iTBS stimulation or sham stimulation once daily for 5 consecutive days. The two treatment sessions are separated by a 5-day washout period. Demographic, MRI, and clinical information of the patients will be collected at enrolment. The CRS-R score will be assessed before and after every session of iTBS and sham stimulation within 2 hours. 32-channel EEG will be performed 20 minutes before and after the first and after the fifth treatment sessions within 30 minutes. The analyses will compare the effects of iTBS and sham stimulation on the CRS-R score and EEG and assess the functional outcomes of all the participants 3 months and 6 months after enrolment. The TMS deliverer is the only investigator who is aware of the grouping results and is required to sign the confidentiality agreement. All other investigators, including attending physicians, nurses, clinical score raters, EEG analysts, and statisticians, are blinded to the allocation.

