## **10.2 Recording and reporting**

Intolerance conditions, as well as seizures, will be dealt with by down-regulating the stimulus intensity, termination of stimulation, or symptomatic management if necessary. During the intervention phase of the study, all SAEs that cannot be excluded as being related to the intervention and intolerance conditions will be collected, fully

investigated, and documented in source documents and CRFs. It is not expected that SAEs related to the intervention will occur after the intervention. In addition, all such events will be reported to the PI and the Data and Safety Monitoring Board (DSMB) as soon as possible (within 24 hours). The DSMB will closely monitor all SAEs for any relationship to the study procedures and protocol and will submit all SAEs to the independent statistician for review.

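### Intolerance is defined by reference to iTBS alone, so sham-period events cannot count and staff described as blinded cannot apply the definition

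*Supplement*

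**What the plan says.** Three sections of the current versions carry the same definition: Protocol V2.0 sections 3.3 and 10.1, and SAP V2.0 section 2.2.4. What counts as intolerance is this: "Any uncomfortable condition due to the iTBS stimulation and needs to be eased by down-regulating stimulus intensity or discontinuation of stimulation". The sentence that opens each of these paragraphs uses a broader name: "Safety outcomes included adverse events, including intolerance to TMS, and severe adverse events".

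On blinding, Protocol V2.0 section 4.1 states: "The TMS deliverer is the only investigator who is aware of the grouping results". It continues: "All other investigators, including attending physicians, nurses, clinical score raters, EEG analysts, and statisticians, are blinded to the allocation". No exception is made there for the PI.

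On recording, section 10.2 says that during the intervention phase "all SAEs that cannot be excluded as being related to the intervention and intolerance conditions will be collected", and that they are to be "investigated, and documented in source documents and CRFs". It adds that "all such events will be reported to the PI and the Data and Safety Monitoring Board (DSMB) as soon as possible", with a limit of 24 hours. Section 14.3 also has the PI review CRFs after every four randomized patients.

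**The concern.** Section 4.1 sets iTBS stimulation against sham stimulation as the two things a patient may receive. A definition that requires the discomfort to be due to iTBS therefore names one arm of the comparison. Two consequences follow.

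The first concerns the safety outcome itself. Under section 7.3 the sham period follows the same procedure as the active period except for the coil angle, so a complaint that leads to stopping could arise in either. Only those in the active period meet the definition.

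The second concerns the blind. Whoever decides that an event is due to iTBS must know which condition was being delivered. The primary outcome, the Coma Recovery Scale-Revised (CRS-R), is scored by raters before and after every session, and EEG segments with artefacts are removed by hand. These judgements depend on the blinding that 4.1 promises, so a reporting rule that carries the allocation beyond the TMS deliverer deserves attention.

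**Working it through.** The plan states no figure on this point, so the check is mainly of the text. The arithmetic only shows scale.

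**1. What can be counted.** Take an event that leads to lower intensity or to stopping.

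| Period | Literal reading (due to iTBS) | Broader reading (intolerance to TMS) |
|---|---|---|
| Active | counts | counts |
| Sham | cannot count | counts |

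The two labels in one paragraph give different event counts.

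**2. Size of the one-sided count.** Inputs: 44 patients (SAP V2.0 section 4), each with both periods, and a per-patient, per-period rate p. The documents give no rate, so p is assumed. Suppose that the true rate is the same in both periods, so that no difference exists. Expected events are 44 × p in each period, but the literal reading records none under sham:

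| Assumed p | Active, recorded | Sham, true | Sham, recorded under the literal reading |
|---|---|---|---|
| 1% | 44 × 0.01 = 0.44 | 0.44 | 0 |
| 2% | 44 × 0.02 = 0.88 | 0.88 | 0 |
| 5% | 44 × 0.05 = 2.2 | 2.2 | 0 |

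The whole recorded difference would come from the definition.

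**3. Who can apply it.** There are two branches.
- A blinded person makes the attribution. That person cannot tell iTBS from sham, so the literal definition cannot be applied.
- The TMS deliverer makes it. The definition can be applied, and an entry then means that the period was active. Section 10.2 sends that entry to source documents and CRFs, and a report to the PI and the Data and Safety Monitoring Board (DSMB).

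The documents do not say which branch is intended.

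**4. How far one record reaches.** In a two-period crossover, knowing that one period was active fixes the other as sham. One record therefore reveals 2 of the 44 × 2 = 88 patient-periods. Section 5 describes randomization without stratification or blocks, so one patient's sequence says nothing about another's through the list.

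**5. Chance that any such record arises.** P(at least one) = 1 − (1 − p)^44, with p the assumed rate in the active period:
- p = 1%: 1 − 0.99^44 = 0.357
- p = 2%: 1 − 0.98^44 = 0.589
- p = 5%: 1 − 0.95^44 = 0.895

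These are chances of at least one intolerance record among 44 patients. They are not chances of unmasking the trial. Each record discloses a sequence only on the literal reading, with attribution by someone who knows the arm.

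**The case against.** The strongest reply is that the wording is loose and not a rule anyone would follow to the letter. The paragraph opens with intolerance to TMS, which fits either condition. A blinded nurse using that label could log an event in either period, and the record would disclose nothing. No passage says who attributes events to iTBS. This stands in part: the literal reading is not the only one. But the sentence that defines the outcome is the narrower one, and it appears in three places. Leaving the choice open is itself a fault, because the two readings give different counts.

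A second reply is that little depends on the count. SAP V2.0 section 7 tests only serious adverse events (SAEs) and states no comparison of intolerance between conditions. That also stands, and it limits the damage to the reporting of a named safety outcome; no planned test is affected.

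A reader might go further and infer that raters, EEG analysts and statisticians are unblinded, or that one record decodes the whole dataset. The documents support neither. Section 10.2 sends intolerance to source documents, CRFs, the PI and the DSMB, and only SAEs to the independent statistician. No section reviewed gives raters, EEG technicians or the trial statistician these entries before scoring or database lock. Decoding the dataset would need one masked condition code shared by all patients and seen alongside the record, and no such code is described. Section 12, on the PI and committees, was not available for this check, so a safeguard stated there cannot be ruled out.

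**Conclusion.** The point holds in a limited form. As written, the definition makes sham-period intolerance zero and so prevents a fair comparison of that outcome between conditions. It also conflicts with section 4.1: blinded staff cannot apply it, and if the TMS deliverer does, the record reveals that patient's active and sham periods to at least the PI.

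The size is modest: one patient's sequence per record and, at assumed rates of 1% to 5%, between 0.44 and 2.2 affected patients expected among 44. The conclusion about the count rests on the literal reading of the definition. The conclusion about disclosure also needs attribution by someone who knows the arm. No effect on CRS-R or EEG results is shown. This is a wording fault worth correcting because the correction is nearly free. It is not evidence that the trial's blinding fails.

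**What to change.** In Protocol V2.0 sections 3.3 and 10.1 and SAP V2.0 section 2.2.4, replace the reference to iTBS as the cause with allocation-neutral wording, for example: *any uncomfortable condition during or after a study stimulation session, in either period, that leads to a lower stimulus intensity or to discontinuation*. Record it by session in both periods on a CRF line that does not name the condition, and have the 24-hour report to the PI likewise omit the allocation.

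How discomfort is managed stays as it is, and so does access to the allocation when safety requires it.

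The cost is one sentence in three places, one CRF line and a small change to the report, with no extra patients or visits. The downside is that some sham-period events will be counted that the present wording excludes.
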